### Participants

Participants will be recruited from HNP, which has collected the health and genetic information of over 50,000 participants [59]. HNP staff will recruit previously enrolled participants (who have consented to be re-contacted) through their email listserv.Our target population is adult men and women of reproductive age (18-44 years old). We expect to enroll approximately 30% racial/ethnic minorities overall. The eligibility criteria include the following: a) ages 18-44 years; b) in good health, not pregnant, free from diabetes or known kidney disease or cancer (these conditions may interfere with EDC metabolism); c) able to understand written and spoken English; and d) willing to complete all study assessments. HNP staffwill obtain onlineinformed consent from all participants and randomly assign them to either the intervention or control group of the trial.The consent form includes the following information: “This study is being conducted by Renown Institute for Health Innovation and Million Marker, a private company, as a study to demonstrate the ability to obtain important exposome data using urine samples. Results from this study may be used to apply for future funding through research grants or sponsor funded studies. As such, each entity may benefit financially if future funding is secured, however, researchers' direct compensation is not dependent on the outcomes of this research. This disclosure is made so you can decide if this relationship will affect your willingness to participate in this study. Renown Institute for Health Innovation is providing their scientific expertise and research staff to conduct this study. Million Marker is contributing the urine kits, data collection via phone app, results, and staff resources, including [name]'s salary, to conduct this study. [name] is the Founder and CEO of Million Marker and is a member of the research study only involved in aggregated data analysis and research publications as a result of the study.”

Participants will be informed of any possible adverse outcomes, with the following statement: “Your participation in this study is non-invasive and there is no risk from providing a urine sample. However, there are risks involved in having your exposure information analyzed and in sharing your exposure information. Your exposure data may reveal that you have high exposure to certain chemicals, such as endocrine disrupting chemicals (EDCs), which may negatively impact your health. You may choose to seek additional healthcare advice or treatment, however any medical advice or treatment that you seek based on your results will be your financial responsibility. As with any database, despite RIHI and MM implementing rigorous privacy and security measures to protect the privacy of your information, there is always a chance that your exposure data, health information, survey responses, and/or personally identifying information may be stolen in the event of a security breach. Although RIHI and MM cannot provide a 100% guarantee that your data will be safe, they have strong policies and procedures in place to minimize the possibility of a breach. In addition to the risks noted above, there may be additional risks to participation that are currently unforeseeable.” Participants can leave the study at any time and will receive monetary compensation for completing study steps.

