## Methods

### Study design

This study is an ongoing collaboration between Million Marker and the Healthy Nevada Project (MM-HNP Study). We will test and compare the effectiveness of 1) EDC exposure report-back (control), and  2) a self-directed online interactive curriculum of EDC EHL material, with access to live coaches and an online forum (intervention). We hypothesize that the self-directed online interactive curriculum with personalized and community support will be more effective (superior) than EDC report-back alone at reducing EDC exposures (behavior change and metabolite concentrations), as well as increasing EDC-specific EHL, readiness to reduce exposures, and well-being. These two arms will be tested in a longitudinal EDC randomized control trial (n=600). Participants will be allocated to intervention groups by the MM team via block randomization, using random-number generation software. The HNP team will generate the allocation sequence and enroll participants. Outcomes for this aim will measure surveyed changes pre- post-interventions in EDC EHL, including EDC-specific knowledge/behavior/attitudes, RtC, well-being, and urine EDC metabolite concentrations. Additionally, we will test a subset of individuals from each intervention arm (*N* = 150 from each group, for a total of
*N* = 300) for clinical biomarkers using a mail-in blood card test. Outcome assessors and data analysts will be blinded to the intervention status of the participants. Additionally, participants will not be aware of their intervention status (i.e. what the other group undergoes).

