**Fig. 1 Fig1:**
[figure not shown]
Timeline of study events for control and intervention groups

Participants will be able to view the results of their Lifestyle Audit online, as well as their test results and reports. These tools will also help participants to self-monitor their behaviors and exposure reduction progress. All participants (control and intervention) will receive a report back of their urinary exposure levels. The control group will receive a list of general recommendations for exposure reduction based on their EDC exposure levels,while the intervention group will receive a more personalized exposure reduction plan based on the information collected in their Lifestyle Audit.

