### Clinical biomarker testing

In addition to reducing EDC exposure via report-back/intervention programs, we will also assess clinical endpoints which may be improved by the reduction of EDC exposures as well as our lifestyle behavioral intervention program. To do this, we have partnered with SiPhox, a direct-to-consumer health and disease biomarker testing company [72]. SiPhox uses blood spot technologies to cost-effectively test a wide range of biomarkers involved in cardiovascular diseases and inflammation (apolipoprotein AI (Apo-AI), apolipoprotein B (ApoB), high-sensitivity C-reactive protein (hs-CRP), high-density lipoprotein (HDL), low-density lipoprotein (LDL), triglycerides (TG)), metabolic disease and diabetes (hemoglobin A1C (HbA1c), insulin), hormones and fertility (estradiol, testosterone, free testosterone, prostate-specific antigen, follicle-stimulating hormone (FSH), luteinizing hormone (LH), prolactin, sex-hormone binding globulin (SHBG), anti-Mullerian hormone, thyroid-stimulating hormone (TSH)), stress (cortisol, DHEA), and cancer (hs-CRP, prostate-specific antigen). These biomarkers can indicate risk for disease as well as the extent of ongoing disease states. Changes in these biomarkers can indicate improvement in health and reduced risk for disease. For example, high levels of high-sensitivity C-reactive protein (hs-CRP) indicates chronic inflammation and contributes to many diseases, including cancer, heart disease, lung disease, chronic obstructive pulmonary disease, chronic kidney disease, Alzheimer’s disease, diabetes, obesity, and high blood pressure. Thus reducing hs-CRP can reduce the risk for these diseases.^3^ Similarly, changes in hormone levels, such as increased testosterone, can indicate increased fertility and male reproductive health [73, 74].

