
### Monitoring

Trial conduct will be closely monitored by the MM and HNP teams to ensure strict compliance with data management and promote study quality. We do not anticipate any risks to the subjects, but any adverse events will be noted.

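### The quoted risk statement calls participation non-invasive although 300 of 600 participants are to give blood, and the Monitoring section denies risks that the statement names

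*Protocol article*

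**What the plan says.** **Risk disclosure.** The Participants section introduces the text with "Participants will be informed of any possible adverse outcomes, with the following statement". The statement opens "Your participation in this study is non-invasive and there is no risk from providing a urine sample". It then names the risk of finding out about high exposure to certain chemicals, the participant's own liability for the cost of follow-up care, and a security breach: "there is always a chance that your exposure data, health information, survey responses, and/or personally identifying information may be stolen". It closes with a catch-all for risks that cannot at present be foreseen.

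**Stated purpose.** The consent excerpt earlier in the same section describes the project "as a study to demonstrate the ability to obtain important exposome data using urine samples".

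**Blood testing.** Study design plans to test 150 participants in each arm "for clinical biomarkers using a mail-in blood card test". Intervention design sends the kits, including the blood kit for the subset, after consent and randomization. Clinical biomarker testing lists the panel and says of it: "These biomarkers can indicate risk for disease as well as the extent of ongoing disease states".

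**Return of results.** Intervention design says "All participants (control and intervention) will receive a report back of their urinary exposure levels". The same paragraph also says that participants can view their test results and reports online.

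**Monitoring.** "We do not anticipate any risks to the subjects, but any adverse events will be noted".

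**Where the full form is.** The SPIRIT checklist (Table 2) points to Appendix 1 for the model consent form, biological specimens, harms and consent provisions. Appendix 1 is not among the documents.

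**The concern.** The statement is offered as the means of telling participants about any possible adverse outcome, and its first clause describes participation as a whole. For those in the blood subset that description does not match the design. They collect blood at home, and the sample is tested for markers that the protocol itself says can reflect existing disease. The only test-result risk named is high chemical exposure, which is different from learning of a possible disease.

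The Monitoring sentence is a second, separate conflict. The article cannot both tell participants that having their exposure information analysed and shared carries risks and say that no risks to them are anticipated.

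What is at stake is the accuracy of what participants are told and the consistency of the protocol that an ethics committee relies on. The trial's estimates, power and analyses are not affected.

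**Working it through.** **Size of the subset**

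- Inputs: 150 per arm and two arms (Study design; Clinical biomarker testing); 600 randomized (Sample size).
- 150 × 2 = 300, the stated total. 300 / 600 = 50%.
- Biomarkers are compared before and after the intervention (Data collection, management, and analysis), so up to 300 × 2 = 600 blood samples.

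**Check on the plan's own figure behind the subset**

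- Inputs (Clinical biomarker testing): paired t-test, two-sided alpha 0.05, power 95%, effect size 0.37, stated n = 97.
- Normal approximation: n = ((1.960 + 1.645) / 0.37)² = 94.9. The exact calculation with the noncentral t gives 96.9, rounded up to 97. This reproduces the stated figure.
- 97 × 1.3 = 126.1 (stated 126), and 126 × 2 = 252 (stated 252).
- So 300 is a deliberate planned number, not a misprint. The sample-size arithmetic has no further bearing on this point.

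**Size of the panel**

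- Counting each marker once: 6 cardiovascular and inflammatory + 2 metabolic + 10 hormone and fertility + 2 stress = 20. The two cancer markers, hs-CRP and PSA, are already counted.
- The quoted consent text mentions none of them.

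**The passages side by side**

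| Point | Risk statement (Participants) | Elsewhere in the article |
|---|---|---|
| Nature of participation | Non-invasive, without qualification | Blood card for 300 of 600 (Study design; Clinical biomarker testing) |
| Specimen named | Urine | Urine for all, blood for a subset (Intervention design) |
| Test-result risk named | High chemical exposure | Markers of disease risk and existing disease (Clinical biomarker testing) |
| Whether risks exist | Yes, several named | None anticipated (Monitoring) |

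**Does other wording rescue the statement?**

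1. The opening sentence deals with urine in its own second clause. The first clause is therefore most naturally read as describing participation generally.
2. The catch-all reaches only risks that cannot now be foreseen. A blood test written into the design can be foreseen.
3. The Discussion section on the need for an exposure reduction intervention explains non-invasive by reference to urine. That supports restricting the word to the urine component.
4. Intervention design places the blood kit after consent and describes no second consent step. The article is a condensed account, so this shows only that none is described.

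**The case against.** The strongest reply is that the article gives excerpts and the consent form itself is in Appendix 1. A blood section or a separate consent for the subset may be there. Expected outcomes and limitations calls the biomarker work exploratory and foresees difficulty in recruiting people to the blood test, which leaves room for a separate invitation. This stands, and it rules out several stronger readings that a reader might infer:

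- **Half the sample consents on a wrong risk description.** This needs the full form, which is not shown.
- **The statement covers only urine and exposure data.** It does not. The breach risk extends to health information, survey responses and identifiers.
- **An abnormal blood result goes to nobody.** The explicit report-back commitment concerns urinary levels, but participants can also view their test results and reports, and the kits are defined to include the subset's clinical biomarkers. The article is unclear on this point, and it may leave the handling of results to the full protocol.
- **Baseline HbA1c undermines eligibility.** The criteria require freedom from diabetes but set no laboratory criterion, so this is speculation.
- **The stated purpose shows that blood was left out of consent.** That excerpt is mainly a disclosure of financial interests, so its silence on blood carries little weight.

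The reply does not remove the conflict in wording. The point rests on what the article asserts: participation is non-invasive, and no risks are anticipated. Blood wording in Appendix 1 would still leave the first assertion wrong for the subset and the second at odds with the statement.

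**Conclusion.** The point holds as an inconsistency in consent and risk wording. The quoted statement is inaccurate for the planned blood subset of 300 of 600 participants (50%, up to 600 samples). The Monitoring sentence contradicts the risks that the statement names, and that conflict exists whatever Appendix 1 contains.

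The documents do not show that consent is invalid for anyone. That would depend on Appendix 1 and on how the subset is recruited, and neither can be seen here. The conclusion assumes that the article quotes the statement accurately and that the blood test goes ahead at the planned size.

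Severity: a correction that should be made, but not a must-fix on present evidence. It becomes one if Appendix 1 is confirmed to contain no blood wording, because recruitment began in July 2024 and study events in September 2024 (Trial status).

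**What to change.** 1. Check Appendix 1 for wording on blood collection and clinical-marker results.
2. **If it is there:** cite it in Participants beside the quoted statement, and limit non-invasive to the urine component.
3. **If it is not there:** amend the consent text so that non-invasive applies to urine only, and so that blood collection and possible abnormal clinical-marker results are named as risks for the subset. The sponsor and ethics committee should decide how to inform blood-subset participants already enrolled.
4. In either case, replace the Monitoring sentence with one consistent with the risks named in Participants.

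Cost: one wording amendment and, in the second case, possibly re-consent of subset participants already enrolled. No added visit, procedure, sample or analysis.

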### Sample size

We will recruit and randomize 600 participants (1:1 male to female). According to previously published research, this has the power to detect estimated effect sizes for 13 endpoints (9 metabolites and 3 survey analyses), [6, 44, 56, 60, 61] from a sample of *n* = 150 participants per arm (i.e., after 50% attrition down from the original *n* = 300 per arm).

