### Previous work

In previous work, [44] participants in the Healthy Nevada Project completed EHL and readiness to change surveys before (*n* = 424) and after (*n *= 174) an EDC exposure report-back intervention (measured via the MM mail-in testing kit). Report-back of results included urinary levels, information about health effects, sources of exposure, and personalized recommendations to reduce exposure. Participants ranged in age from 18-61, were primarily women (75%), and white (79%). EHL was generally very high at baseline. Higher EHL knowledge was shown among older participants (*p* = 0.02) and those self-rated in poorer health (*p *= 0.007). EHL behaviors increased after report-back (*p *= 0.003).

For readiness to change, 72% were already or planning to change their behaviors. Women were generally in earlier stages than men (p=0.071), but post-intervention, women increased their readiness (p=0.053), while men decreased (p=0.007). When asked what challenges they faced in reducing exposure, 79% cited not knowing what to do. This dropped to 35% after report-back. Participants with higher propylparaben were younger (p=0.03), women and participants who rated themselves in better health had higher levels of some phthalates (p=0.02-0.003 and p=0.001-0.003 respectively). After report-back, monobutyl phthalate decreased among the 55 participants who submitted a second urine test (p<0.001). Of the 50 participants who completed final surveys, 50% reported now using non-toxic personal products, 44% were using non-toxic household products, 20% dined out less, 32% ate less packaged food, 40% used less plastic, and 48% read product labels more.

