## Intervention

### The Millon Marker (MM) test kit and report-back

The MM EDC testing panel consists of 13 metabolites, assessing exposure to EDCs that are commonly found in household and personal products. These chemicals are found in over 90% of the US population (at any one time) [5, 15, 21, 22, 62].

Consented participants will be mailed the MM *Detect and Detox* kit. Upon receipt, participants in the intervention group will 1) engage in a Zoom call with a MM coach to complete a comprehensive 24-hour food/product Lifestyle Audit the day before their urine sample collection, 2) collect first void urine sample the next morning, 3) send back samples via FedEx, 4) receive results as well as personalized recommendations for products and lifestyle changes to reduce EDC exposures, 5) follow the recommendations and make changes to reduce exposures, 7) test again after 3 months. Participants in the control group will complete Steps 2-7, and will receive a report-back with more generalized recommendations. Participants will be guided through this journey from our online instructions, online video tutorials, extensive educational materials, and email communication.

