For the analysis plan, we will examine the distribution and concentrations of each of 13 chemical analytes in urine to determine geometric means, medians, percentiles and ranges of exposures. We will compare the percentiles with those reported in the NHANES study. We will include BMI, age, gender, diet, education and household income as covariates. Participants’ dietary patterns will be captured prior to sample collection by looking at their consumption of packaged food and times eating out as these are important culprits of EDC exposures. We will conduct an intent-to-treat analysis. The primary outcomes are the pre-post (first and second tests) differences in specific gravity-adjusted concentration levels per analyte. Clinical biomarkers measured before and after the intervention will also be compared to assess improvement in health and reduced disease risk. We willassess changes in participants’ EHL, RtC and well-being before and after the interventions as well. We will first generate summary statistics on participants’ responses. Changes will be calculated based on paired values of individual responses.

For all analyses, data will be reviewed to ensure assumptions are not violated. If outcomes are not sufficiently normally distributed for parametric tests to be valid, nonparametric tests will be conducted. If needed, variables with response categories with too few participants will be combined. Attrition analyses will be run to compare demographic variables between participants who completed post-test surveys and those who did not.

Summary data and associations between demographic variables and EHL, RtC, well being, EDC metabolites, and clinical biomarkers will be analyzed for all participants with pre-test survey data. Independent sample t-tests, one-way ANOVAs, Chi-square tests, and Spearman’s rank correlations will be run as appropriate. Changes from pre-test to post-test comparing differences between the intervention and control groups, will be analyzed for participants who completed both surveys using regression analyses, controlling for significant demographic variables.

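### The sample-size statement miscounts its endpoints (9 + 3 is 12, not 13), covers only 9 of the 13 primary analytes, and assumes an attrition rate that the article's own figures do not support

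*Protocol article*

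**What the plan says.** The Sample size section opens with "We will recruit and randomize 600 participants (1:1 male to female") and continues, citing published work, that "this has the power to detect estimated effect sizes for 13 endpoints (9 metabolites and 3 survey analyses"). The analysable number is 150 per arm, "after 50% attrition down from the original *n* = 300 per arm". The section gives no effect size, standard deviation, alpha or power.

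The test kit section states that "The MM EDC testing panel consists of 13 metabolites". The section on data collection, management and analysis names the analytes (they count to 13), plans to describe "each of 13 chemical analytes in urine", and then says: "The primary outcomes are the pre-post (first and second tests) differences in specific gravity-adjusted concentration levels per analyte".

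On retention, the Previous work section reports that participants in the same parent cohort completed "surveys before (*n* = 424) and after (*n *= 174) an EDC exposure report-back intervention", and that "monobutyl phthalate decreased among the 55 participants who submitted a second urine test". It does not say how many people were offered a second urine test.

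The Clinical biomarker testing section has its own calculation: 97 participants for a paired t-test (effect 0.37, two-sided alpha 0.05, 95% power), multiplied by 1.3 for attrition to give 126 per group. It concludes that the planned 150 per group is enough.

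**The concern.** This short paragraph is the only justification the article gives for the size of the main comparison. Two of its elements conflict with the rest of the article. First, the endpoints said to be powered do not sum to their stated total and do not match the set of primary outcomes. A reader cannot tell which primary analytes the claim is about. Second, the 150 per arm depends on a 50% attrition rate. The sponsor's own retention record was worse on surveys, and the same trial uses a much milder allowance elsewhere.

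At stake is whether anyone can say what between-arm difference the trial could detect on its primary outcomes. These need a second urine sample, so retention to that sample drives the analysable number.

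**Working it through.** **1. Endpoint count.** Stated total 13; stated parts 9 metabolites and 3 survey analyses.
- 9 + 3 = 12, one short of 13.
- Primary analytes: 13 (panel size, named list and analysis text agree). Covered by the claim: 9. Not covered as written: 13 − 9 = 4, not identified.
- All primary analytes plus the three surveys: 13 + 3 = 16.

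No single misprint repairs this. Reading it as 9 + 4 restores the total of 13 but still leaves four primary analytes out. Reading it as 13 metabolites covers the primary set but makes the total 16.

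**2. The plan's attrition arithmetic.** 300 × (1 − 0.50) = 150 per arm. This reproduces. Only the choice of 50% is in question.

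**3. The earlier study's retention.**
- Surveys: 174 / 424 = 41.0% retained, 59.0% lost.
- Applied to this trial: 300 × 174/424 = 123 per arm.
- To keep 150 per arm at that rate: 150 / 0.4104 = 365.5, so 366 per arm, 732 in total. This shows the size of the gap; it is not a recommendation.
- Second urine: 55 people, denominator not stated. 55 would meet 50% retention only if the denominator were at most 55 / 0.5 = 110.

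**4. Detectable difference between arms.** The article gives no alpha or power for this comparison, so 80% power and two-sided 0.05 are assumed. With n analysable per arm, d = (1.960 + 0.842) × √(2/n).

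| Attrition | n per arm | d, normal formula | d, t-test |
|---|---|---|---|
| 50% | 150 | 2.802 × 0.1155 = 0.323 | 0.325 |
| 59% | 123 | 2.802 × 0.1275 = 0.357 | 0.359 |

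The detectable difference rises by about 10% (0.359 / 0.325 = 1.10).

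**5. The biomarker subset.**
- The plan's figure reproduces: for a paired t-test with d = 0.37 and two-sided 0.05, n = 97 gives power 0.950 and n = 96 gives 0.948.
- 97 × 1.3 = 126.1, reported as 126; two groups make 252. Also reproduced.
- Going from 126 to 97 is a loss of 1 − 1/1.3 = 23%, against 50% in the Sample size section.
- At 50%, 150 × 0.5 = 75 per group, short of 97 by 22. By the same formula, power at n = 75 is 0.885 rather than 0.95.
- 150 per group keeps 97 only while attrition is at most 1 − 97/150 = 35%.

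**The case against.** The mismatch may be a misprint. The section cites five sources, and the full protocol is available on request; effect sizes and standard deviations may well be there. A condensed article need not repeat them. That stands, and it means nobody can say from this document that the four remaining analytes were never considered. It does not remove the error: a wrong total and a powered set that differs from the primary set are faults in what is printed, not omissions.

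On attrition, the earlier study was a report-back study with a different design, and its 59% is survey loss, not urine loss. This trial pays for completed steps, requires willingness to complete all assessments, and has coaches contact the intervention arm. The earlier figure is therefore evidence about 50%, not a refutation of it, and the resulting shift in detectable effect is modest.

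On the biomarker subset, one could suppose that its 150 per group is already a number of completers. The text does not read that way: 150 is compared with 126, which already includes the attrition allowance, and baseline kits go out before attrition is known. The article does call the biomarker assessment exploratory, which lowers the stakes there.

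Three stronger readings are tempting but not supported:
- That the trial is underpowered. With no effect size, alpha or power stated for the main comparison, there is no claim to test.
- That second-urine retention was 55 out of 424. The 424 counts baseline surveys, and the number offered a second kit is not given.
- That one significant analyte out of 13 would count as success. The article does not say so, and its checklist refers the statistical methods to an appendix that is not shown and may hold a multiplicity rule.

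**Conclusion.** The concern holds as an internal inconsistency that should be fixed. As written, the endpoint total is wrong by one and the power claim reaches 9 of 13 primary analytes. The 50% attrition is more favourable than the 59% survey loss, the clearest retention rate the article reports. It also disagrees with the 1.3 factor used for the biomarker subset, where 50% would leave 75 against a stated need of 97. The claim of adequate power is unsupported as stated; it is not shown to be false.

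The size is modest where it can be measured: 123 rather than 150 per arm, and a detectable standardised difference of about 0.36 rather than about 0.33. This assumes that survey loss carries over to this trial, and uses 80% power and two-sided 0.05. The effect of second-urine retention, which matters most for the primary outcomes, cannot be sized until its denominator is known.

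**What to change.** Revise the Sample size and Clinical biomarker testing sections together:

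1. Correct the count. List which of the 13 primary analytes and which survey analyses the power claim covers, with the effect size, alpha and power used for each between-arm comparison.
2. Use one attrition assumption in both sections, or explain why they differ, and justify it against the earlier study. If 50% is kept, restate the biomarker calculation for 75 per group.
3. State the detectable between-arm difference at 50% and at 59% attrition (150 and 123 per arm; about 0.33 and 0.36 on the assumptions above).
4. Report how many people in the earlier study were offered a second urine test, then add the detectable difference over a range of second-urine retention.

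The cost is recalculation and wording, with no added enrolment and no change to the primary outcomes. The one downside is that the stated detectable effect becomes slightly less favourable.
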